## Abstract

**Background:**

Lower limb **s**trengthening, especially the quadriceps training, is of much necessity for patients with knee osteoarthritis (KOA). Previous studies suggest that strengthening of the hip muscles, especially the hip abductor, can potentially relieve the KOA-associated symptoms. Nevertheless, the effects of quadriceps combined with hip abductor strengthening remain unclear. Therefore, the current randomized controlled trial is designed aiming to observe whether quadriceps in combination with hip abductor strengthening can better improve the function and reduce pain in KOA patients than quadriceps training alone.

**Methods:**

A total of 80 subjects with symptomatic KOA will be recruited from the communities and hospital outpatient, and will be randomly assigned to the experiment group (Quadriceps-plus-hip-abductor-strengthening) or the control group (Quadriceps-strengthening). Specifically, participants in the experiment group will complete 4 exercises to train the quadriceps and hip abductor twice a day for 6 weeks at home, while those in the control group will only perform 2 exercises to strengthen the quadriceps. Besides, all patients will also receive usual care management, including health education and physical agent therapy when necessary. Knee pain will be measured using the Visual Analogue Scale (VAS) at baseline, in every week during the course of treatment, as well as 8 and 12 weeks after randomization. Furthermore, knee function will be measured using the Western Ontario and McMaster Universities Osteoarthritis Index (WOMAC) scale, and the quality of life will be measured using the MOS Item Short-form Health Survey (SF-36). In this study, several simple tests will be applied to assess the objective function. All the assessments except for VAS will be carried out at baseline, and in the 6th, 8th and 12th weeks respectively.

**Discussion:**

Our findings will provide more evidence for the effects of hip abductor strengthening on relieving pain and improving function in KOA patients. Hip abductor strengthening can be added into the muscle training program for KOA patients as a supplementary content if it is proved to be effective.

**Trial registration:**

The current study has been registered with the Chinese Clinical Trials Registry (the registration number is ChiCTR-IOC-15007590, 3rd December, 2015).

## Background

Knee osteoarthritis (KOA) is one of the most common chronic progressive, degenerative and debilitating diseases among the elderly [1]. KOA patients mostly suffer from progressive stiffness and knee pain. Gradually, they have some difficulties in performing daily activities, such as walking, squatting, climbing and doing housework, as the disease progresses [2]. Moreover, the KOA-induced pain and disability will impair their independence and remarkably reduce their quality of life, thus posing a heavy burden on both the families and the society [3]. Generally, the high prevalence, disability rate and medical expenses of KOA have gradually attracted extensive attention from the public [4].

KOA is a chronic progressive and debilitating disease; however, effective fundamental treatments are lacking at present. The existing clinical treatment strategies for KOA aim to relieve pain and symptoms, as well as to delay disease progression, including pharmacological strategies (such as analgesics, non-steroidal anti-inflammatory drugs, corticosteroids and cartilage protecting agents), non-pharmacological strategies (physiotherapies like ultrasonic treatment, acupuncture, patient education, weight loss, exercises and sports support) [5, 6], and surgical strategies (such as replacement of knee for end-stage KOA) [7]. Certainly, these treatments are helpful; nonetheless, some of them may be associated with many potential side effects and are uneconomical. In addition, some of them may be inconvenient for patients requiring frequent hospital visits, which will inevitably add to additional costs. It is noteworthy that, the latest guidelines for KOA have paid ample attention to some non-pharmacological strategies in disease management [5, 6, 8], particularly exercise rehabilitation and sports support.

A variety of exercises have been proposed in literature to treat KOA, including aerobic exercises such as cycling or walking, as well as some targeted exercises like strengthening of particular muscles, and some exercises targeting flexibility. To the best of our knowledge, studies investigating the effects of muscle strengthening on KOA patients mostly focus on the quadriceps [9]. Meanwhile, studies also find that quadriceps strengthening contributes to relieving pain, improving body function as well as quality of life of patients, and delaying disease progression. Furthermore, it is also characteristic of its safety and economical efficiency, which are extremely important for patients. Therefore, such treatment is unanimously recommended in various guidelines.

However, the lower limb represents a whole chain of motion, and changes in the biomechanical environment of the hip, such as in the muscle strength around the hip, may also affect the knee joint. As is discovered in recent studies, some knee diseases, such as patellofemoral pain syndrome [10, 11], iliotibial band syndrome [12], and noncontact anterior cruciate ligament injuries, are related to the strength of muscles around the hip. Notably, the mechanical and kinematic parameters of hip movement in KOA patients are quite different from those in the normal control group [13–15]. In the meantime, some latest studies also propose that, KOA patients are suffering from decreasing hip abductor muscle strength [16, 17]. Specifically, results from a recent cohort study suggest that, people having a smaller external hip adduction moment (in other words, a weaker hip abductor) are undergoing a faster KOA progression [18]. Moreover, a few studies find that, hip abductor strengthening may potentially alleviate pain and improve the overall functions of these patients [19–21]. However, it can hardly decrease the knee load, as is measured by the knee adduction moment [20]. Nonetheless, the efficacy of hip abductor strengthening has not been fully confirmed by original studies yet, which has prevented the routine prescription of such exercises for KOA patients.

Given that hip abductor strength may potentially affect knee load, it is supposed in the current study that quadriceps combined with hip abductor strengthening may be superior to quadriceps strengthening alone for KOA patients. Thus, the current study is thereby designed on this basis, aiming to determine whether patients receiving quadriceps combined with hip abductor strengthening can attain more functional improvement, more pain relief and higher quality of life than those undergoing quadriceps strengthening alone.

## Methods

### Design

The current study is a single-blind randomized controlled trial, in which patients with KOA will be randomly divided into quadriceps-plus-hip abductor-strengthening group and quadriceps-strengthening group (Fig.1). Importantly, physicians carrying out the assessments will not be informed of the group situation.

**Fig. 1 Fig1:**
[figure not shown]
Trial protocol

### Study population and allocation

A total of 80 KOA patients will be recruited from the outpatient of the Affiliated Hospital of Southwest Medical University, as well as from some communities in the city by means of advertisements. The inclusion criteria are as follows: those with osteoarthritis in at least one knee according to the American College of Rheumatology Classification Criteria established in 1995 [22]; those aged over 50 years; those with the self-reported average knee pain > 2.0 and < 7.0 measured by the Visual Analogue Scale (VAS) for most days in the month; and those with the Kellgren-Lawrence grade (K-L grade) for KOA of II-IV. KOA will be confirmed through physical examinations and radiography. For participants with bilateral KOA, the more seriously affected side (as identified by K-L grade of KOA and the pain intensity) would be selected as the affected leg.

In the meantime, the exclusion criteria are shown as follows: patients with the age of ≥70 years; those undergoing hip or knee muscle training in the past 4 weeks; those with obvious knee varus or valgus deformity; those who have taken oral corticosteroid within the last 4 weeks or intraarticular corticosteroid injection within the last 3 months; those with systemic arthritic conditions; those who had undergone tibial osteotomy, hip or knee joint replacement, or other surgeries of knee or hip joint; and those with any other neurological, muscular or joint diseases that may affect the lower limb function.

Patients will be recruited in strict accordance with the inclusion and exclusion criteria, and will be subsequently assigned randomly into the Quadriceps-plus-hip-abductor-strengthening group (experiment group) and the Quadriceps-strengthening group (control group) at the ratio of 1:1. Specifically, the randomization sequence will obtained by an independent researcher not taking part in the treatment or assessments using the random number function in Excel. Allocation will be hiden in serial number, with opaque envelopes placing in the central location. In addition, another researcher participating in the study will then open the envelopes in sequence after patient recruitment and baseline assessment.

### Interventions

All participants will receive routine care management for KOA, including health education and physical agent therapy when necessary.

As some guidelines suggested, all KOA participants in both groups will undergo the Quadriceps-strengthening training composed of 2 exercises designed to strengthen the quadriceps. The first exercise is straight leg raise, to be specific, patients lie in supine position, and keep their legs straight with a resistance band placed just proximal to the ankle of the affected limb. Afterwards, they raise the affected leg to the heel 25-30 cm away from the bed, stay in this position for 5–10 s based on their own abilities, and then slowly lay down. The second exercise is multi-angle static exercise. Briefly, patients sit on their seats with a resistance band positioned proximal to the ankle, and contract their quadriceps isometrically for 5–10 s when their knees are flexed at the angles of 0°, 30°, 60°, 90° and 120°, respectively.

Correspondingly, the experiment group will receive Quadriceps-plus-hip-abductor-strengthening training, which is constituted by 2 more exercises simultaneously to strengthen the hip abductor. One is lateral leg raise, in brief, the patients lie down on bed on the unaffected side, with the resistance band positioned around the distal thigh of the affected limb. Later, they raise the above lower limbs upwards for about 30 degrees, stay for 5–10 s, and slowly lay down. The other exercise is pelvic lift training, specifically, patients stand single-leg off the side at a 10-cm step. Later, they begin with the other limb that is lower than the step level, and contract the stance-limb hip abductor to raise the free leg to the step level while keeping the stance knee extended.

Patients will be required to carry out each exercise for 10 repeats at home as a set, for 3 sets each time and twice a day for 6 weeks altogether. Qualified physiotherapists who have attained the physical therapist’s certification with over 5 years of experience will be trained beforehand, so as to instruct and guide patients in carrying out these exercises. All exercises are standardized; however, the resistance for each movement should be decided according to the practical situation of each patient. As a result, all participants will have to visit the physiotherapists in the Affiliated Hospital of Southwest Medical University once a week for 6 weeks, so as to learn the exercises and adjust the training intensity. Typically, progression to a greater resistance level is possible when participants can perform 20 repeats of a given exercise without fatigue. Moreover, graded resistance elastic bands will be supplied to all participants who are also given a booklet with detailed description and pictures of the exercises, as well as a form on which they can record their completion everyday. Only those who have completed 80% of the target can be considered eligible and enrolled in the final statistics. Finally, all follow-up assessments will be assessed by a blinded physiotherapist.

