### Statistical analysis

Statistical analyses will be performed following the per-protocol (PP) analysis and intention-to-treat (ITT) analysis. Typically, PP analysis would be conducted if no participants have dropped out of the trial for any reason. In addition, the rule of last-observation-carried-forward will be applied for the missing data when performing ITT analysis. Additionally, baseline data will be analyzed and adjusted using the covariance analysis if no statistically significant differences between two groups and a possibility of covariance of baseline data are found. Categorical data, such as gender or those expressed as frequencies (%) will be analyzed using chi-square test or Fisher’s exact test. Non-parametric statistical tests will be applied for data not conforming to normal distribution. In addition, statistically significant differences in intra-group and intergroup data will be analyzed by repeated measure analysis of variance. All statistical analyses will be performed using the SPSS 19.0 statistical software by a statistician blinded to the allocation. The significance level is set at 5%.

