### Safety

All exercises adopted in this study are very safe and harmless, especially under the guidance of physiotherapists. However, all expected or unexpected adverse events deriving from this study, such as muscle strain or ache, will be recorded and monitored. Moreover, patients subjected to harm from this study will receive free treatment, and any differences in safety between the two groups will be reported by researchers as a part of the results.

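### The 80% completion rule for entering the final statistics conflicts with the planned ITT analysis and is not confined to the per-protocol set

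*Protocol article*

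**What the plan says.** The Interventions section describes home exercise with weekly physiotherapist visits. Patients receive "a form on which they can record their completion everyday", which is the only completion record described. The section then sets the entry rule: "Only those who have completed 80% of the target can be considered eligible and enrolled in the final statistics".

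The Statistical analysis section says: "Statistical analyses will be performed following the per-protocol (PP) analysis and intention-to-treat (ITT) analysis". It fills missing values in the ITT analysis by last observation carried forward. It gives the PP analysis no adherence criterion and attaches a different condition: "PP analysis would be conducted if no participants have dropped out of the trial for any reason". It does not say which of the two analyses is primary.

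The arms have different targets. The abstract assigns four exercises to the experiment arm; for the other arm it states that "those in the control group will only perform 2 exercises to strengthen the quadriceps". The amount per exercise is the same in both arms: ten repeats to a set, "for 3 sets each time and twice a day for 6 weeks altogether". The primary outcome (Outcomes section) is VAS pain in week 6, the last week over which completion is counted.

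**The concern.** Although worded as eligibility, the 80% rule is an exclusion after randomisation. The envelope is opened after recruitment and baseline assessment (Study population and allocation), and completion is known only at the end of the exercise period. If the rule governs the final statistics, the groups compared are no longer the randomised groups.

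This matters more here because 80% of the target is a larger amount of exercise in the experiment arm. The Safety section itself gives muscle strain or ache as examples of possible adverse events. If pain or strain makes patients fall short, and more of them do so in the arm with more exercises, exclusion depends on both the arm and the outcome. A team that analysed only adherent patients could say that it had followed the Interventions section, and a team that analysed everyone could say that it had followed the Statistical analysis section. The choice would be open after the data are seen.

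**Working it through.** **1. The two sections side by side.** Interventions: only patients at 80% or more enter the final statistics. Statistical analysis: ITT and PP, with imputation under ITT. An ITT set contains all randomised patients whatever their adherence, so an adherence filter on the final statistics cannot apply to it. The conflict would disappear if the rule defined the PP set only, but Interventions does not mention PP, and Statistical analysis ties PP to the absence of dropouts.

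**2. Targets by arm** (abstract and Interventions; 6 weeks = 42 days).
- Control: 2 × 10 × 3 × 2 = 120 repeats a day; × 42 = 5,040; 80% = 4,032.
- Experiment: 4 × 10 × 3 × 2 = 240 repeats a day; × 42 = 10,080; 80% = 8,064.
- The ratio is 2.0 in exercises, sets and repeats.
- The multi-angle exercise uses five knee angles. If each repeat counts as five contractions, control has (10 + 50) × 6 × 42 = 15,120 and experiment (10 + 50 + 20) × 6 × 42 = 20,160, a ratio of 1.33.

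**3. The plan's own sample size** (difference 2.0, SD 2.5, two-sided 5%, power 90%). n = 2 × [2.5 × (1.960 + 1.282) / 2.0]² = 32.8, so 33 per group, as stated. The total of 80 follows from 33 × 1.2 = 39.6, so 40 per arm.

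**4. Size of a possible selection bias.** The protocol gives no adherence by arm, so these inputs are assumptions. Take latent adherence and week-6 VAS as bivariate normal with correlation −ρ, SD 2.5 and no true effect. If a proportion p is retained, mean VAS among those retained shifts by −ρ × 2.5 × λ(p), where λ(p) = φ(Φ⁻¹(1 − p)) / p.
- λ(0.65) = 0.570 and λ(0.85) = 0.274; the difference is 0.296.
- ρ = 0.3: −0.3 × 2.5 × 0.296 = −0.22 VAS points.
- ρ = 0.5: −0.5 × 2.5 × 0.296 = −0.37 VAS points.

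A negative sign favours the experiment arm. A wider range, with control completion 90%, experiment completion 80% down to 60%, and ρ from 0.2 to 0.5, gives −0.08 to −0.56 points and a two-sided type I error of 5.2% to 14.8%. If completion is equal in the arms, or ρ = 0, the bias is 0 and the type I error stays at 5%.

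**5. Power for 2.0 points, SD 2.5** (two-sample t-test).

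| Analysed per arm | How it arises | Power |
|---|---|---|
| 40 and 40 | all randomised | 94.2% |
| 32 and 32 | 20% lost | 88.3% |
| 25.6 and 25.6 | 20% lost, then 20% of the rest below the threshold | 80.1% |
| 26 and 34 | 65% and 85% of 40, as in step 4 | 85.5% |

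The third row is a different scenario from the bias calculation. The fourth row uses the same retention rates as step 4.

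**The case against.** The strongest reply is that an 80% completion threshold is an ordinary PP criterion and that the sentence is probably a misplaced PP definition. An ITT analysis is expressly planned, with its own imputation rule. A reader might infer that the protocol abolishes ITT; it does not. What stands is that the scope of the rule is not stated and that the one condition given for PP is a different one. Even on the kindest reading, the sentence needs the same correction.

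The second reply is that differential selection is not documented. The threshold is the same proportion in both arms, resistance is set for each patient and adjusted at weekly visits, and no expected adherence is given. This stands in full. The direction is also open: patients who stop because they feel better would push the bias the other way. A reader might infer that the rule does favour the experiment arm, but that follows only under the assumptions in the working.

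Two further inferences are not supported. One is that exclusions must exceed the 20% dropout allowance: the Sample size section does not say whether that 20% includes non-adherent patients. The other is that exercise-related harms would be hidden. The Outcomes section schedules adverse effects at every visit after baseline and has them recorded for each participant, and the Safety section commits that "any differences in safety between the two groups will be reported by researchers as a part of the results". Only a clarification is needed there.

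**Conclusion.** The point holds as a contradiction about the analysis set. The completion rule in Interventions and the ITT analysis in Statistical analysis cannot both be followed as written, and nothing in the protocol settles which one governs the primary comparison. It should be fixed before analysis because it decides who is counted for the primary outcome. It is not a matter left to a statistical analysis plan: the protocol states the rule itself.

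The bias is a risk, not an established fact. It is about 0.2 to 0.4 VAS points at the assumed 65% versus 85% retention and correlation of 0.3 to 0.5. That is under a fifth of the 2.0-point design difference (0.37 / 2.0 = 18%), and it is zero if completion is equal or unrelated to pain. The power loss is also conditional: from about 88% at 32 per arm to about 80% at 25 to 26 per arm, and only if adherence exclusions come on top of the 20% dropout.

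**What to change.** - **Interventions:** delete the sentence as a rule for entering the final statistics.
- **Statistical analysis, primary:** state that the primary analysis includes all randomised patients in their allocated group, whatever their adherence.
- **Statistical analysis, PP:** use the 80% threshold only to define a supportive PP set, in place of the condition that nobody has dropped out.
- **Reporting:** give adherence by arm, stating the unit in which the target is counted.
- **Safety:** confirm that the completion rule does not apply to the adverse-event comparison.

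The cost is wording only, with no additional patients or data. The ITT estimate may be somewhat smaller than one from adherent patients alone.

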### Outcomes

Participants will be assessed by other physiotherapists blinded to the group allocation at different time points based on different assessments shown in Table 1. Additionally, baseline age, gender, symptoms, disease severity (K-L grade), duration, previous treatment and medication will be recorded using a questionnaire (in week 0). The primary outcome is the overall pain assessed using VAS in the 6th week, while the secondary outcomes include the overall function measured by the Western Ontario and McMaster Universities Osteoarthritis Index (WOMAC), as well as the quality of life assessed by MOS Item Short-form Health Survey (SF-36), and several functional tests.

**Table 1 Tab1:** Schedules for follow-up assessments and date collection

Assessments	Baseline	Active strengthening at home						Follow-up	
	Week 0	1st week	2nd week	3rd week	4th week	5th week	6th week	8th week	12th week
VAS for pain	√	√	√	√	√	√	√	√	√
WOMAC	√						√	√	√
SF-36	√						√	√	√
FTSST	√						√	√	√
Step test	√						√	√	√
Stair ascent/descent task	√						√	√	√
Figure-of-8 Walk Test	√						√	√	√
Adverse effects		√	√	√	√	√	√	√	√

The overall pain intensity in the involved knee within the past 1 week will be self-measured by patients using the VAS, with terminal descriptors ranging from 0 (no pain) to 10 (maximal pain). Meanwhile, the overall function of patients will be assessed adopting WOMAC, a disease-specific scale with high reliability and validity [23]. WOMAC is comprised of 24 items assessing pain (scored 0–20), stiffness (scored 0–8) and physical functions (including personal care, walking, sitting, lifting, sleeping, standing, social life and travelling) (scored 0–68). Every item is rated on a scale of 0–5, with a higher score indicating a worse symptom. Moreover, the quality of life will be measured by SF-36 constituted by eight dimensions, including mobility, pain and discomfort, daily activities, depression and anxiety, and self-care [24].

Furthermore, the Five Times Sit to Stand Test (FTSST) is used as a simple objective test of lower limb function [25]. To be specific, participants sit on an armless chair with their backs resting against the chair; later, they will be asked to stand up straight and sit down without touching the chair back each time. The test is accomplished upon the fifth time of returning to sitting, and the time spent will be recorded as a result. Besides, the step test is also employed to measure the standing balance [26]. In brief, participants stand barefoot on the diseased leg facing a 15 cm step; subsequently, they step the opposite foot on and off the step as quickly as possible. The frequency completed within 15 s will be recorded as a result, and a higher score indicates a better standing balance function. At the same time, the stair ascent/descent task [27] is also adopted in the current study, in which all participants will be invited to climb up and down a line of stairs, with eight steps one time at their usual speed. The time spent will be recorded as a result, and a longer time suggests a poorer physical function. In the Figure-of-8 Walk Test, the time that participants take to walk a path around 2 cones that is placed 1.5 m apart will be recorded [28]. Patients will be asked to stand in the middle of the 2 cones initially before they walk in a continuous figure-of-8 pattern around the cones. Finally, they will be asked to stop at the location where they begin, and the time spent will be recorded.

Moreover, the adverse effects, medication and other therapies in each participant over the course of trial will be recorded by themselves.

